### Secondary outcome measures

#### Parent-reported proxy child physical activity

In addition to objective PA assessments for children described earlier, a secondary outcome includes child PA measured via parent proxy self-report. Specifically, parents are asked to report their child’s physical activity as well as family-co-activity (both structured and unstructured) at all measurement occasions (baseline, 6 weeks, 3 months, and 6 months) using an adapted Godin Leisure-Time Exercise Questionnaires [72] modified for co-activity [60, 73]. This instrument is included in addition to objectively measured PA because the measurement methods are not equivalent but can be complementary: self-report is distinct as it allows for the assessment of volitional PA [74] and a more focused report of PA specifically as a family. While parent proxy measures are certainly less accurate than accelerometry, this measure has shown sensitivity to change in intervention and predictive validity in observational data [73].

#### Parental co-activity habit

At all measurement occasions (baseline, 6 weeks, 3 months, and 6 months), parental co-activity habits for child PA will be measured with an adapted self-reported habit strength index [75] which includes the self-reported behavioral automaticity index subscale [76], both of which have demonstrated excellent reliability and validity in self-reported and objective PA assessment [77]. These measures have been used in prior research assessing habit of parental support within M-PAC [30]. Therefore, the scale follows the same form but was slightly modified for co-activity and thus the 12 items are as follows: “regular physical activity with my child is something I do... frequently, automatically, etc.” answered on a five-point Likert scale.

### Tertiary outcome measures

#### Parental physical activity

The tertiary outcome of parental PA is measured both by self-report and seven-day accelerometry at all assessment occasions (baseline, 6 weeks, 3 months and 6 months). Accelerometry will be measured in a similar fashion to the methods outlined above. Namely, parents are instructed to wear the Actigraph wGT3X-BT for 7 days a week for a minimum of 10 h a day, remove it at night and for water-based activities, and note the details of the wear in a logbook. Activity will be assessed by measuring several variables, including duration (total minutes worn, total movement counts/day, total minutes of sedentary, light, moderate-vigorous day), frequency (bouts of sedentary, light moderate-vigorous/day), and intensity. To calculate these variables data will be collected in 10 s intervals and reintegrated into 60 s epochs to align with the methods of Troiano et al., [78]. Non-wear time will be determined using the algorithm from Troiano et al., [78] and will be subtracted from total wear time. As per recommended best practice [79, 80], parents need at least 4 days with 10 h of valid wear per week. Accelerometers have demonstrated reliability and validity when worn for ≥4 days [81–83]. The MVPA of adults will be evaluated as change from baseline and determined using frequently applied cut points [66] validated for adults [78] which classify MVPA as 2020 counts per minutes (CPM) and above. Again, the research team is mindful of the rapidly evolving nature of accelerometry analysis and therefore we will be responsive to the most validated cut-point norms in the field at the time of study closure.

As a secondary self-reported parent PA outcome measure, the Godin Leisure-Time Exercise Questionnaire (GLTEQ), is employed [72, 84] which assesses the frequency and duration of mild, moderate, and strenuous activity performed during free time in a typical week in an open-ended manner. A total weekly MVPA score will be calculated by multiplying the frequency by the duration.

#### Parent-child co-activity

Parent-child co-activity is assessed at all measurement occasions via self-report (with a modified GLTEQ; 71) and objectively via accelerometry. Accelerometry will be measured as discussed in the outcomes above and tagged with the child to assess co-activity. A relatively new feature of the accelerometer is the ability to determine the presence of other nearby people (i.e., parent or child), who are also wearing accelerometers. This Bluetooth-enabled feature allows for the objective assessment of co-activity between parent and child. In this method, “beacon” devices broadcast their serial number and “receiver” devices are set to search for the signal once per minute. The receivers then store a log of proximity detection information, recorded as a received signal strength indicatior (RSSI). In the present study, the child’s monitor is set as the “receiver” and the parent’s monitor (secondary outcome) is set as the “beacon”. Every 60 s where the monitors are in close proximity will be “tagged” and recorded in the memory of the child’s monitor, which will be later linked to time-stamped data of the parent. According to ActiGraph [85], accelerometers communicate via Bluetooth when in close proximity indoors, which is a maximum of 10–20 m, and close proximity outdoors, which is a maximum of 100 m. One study examining Bluetooth-enabled accelerometers found acceptable validity for determining whether parents and children are in close proximity [86]. Another study examining the validity and reliability of the feature found proximity detection with Bluetooth-enabled accelerometers was reliable in controlled settings and had reasonable rates of detection during free-living conditions albeit only when in close proximity [87].

#### M-PAC constructs for parent-child co-activity

Beyond habit, the additional M-PAC constructs are framed for parent-child co-activity. These measures include motivational (instrumental attitude, affective attitude, and perceived capability), regulatory (planning), and reflexive (automaticity, identity) elements. Intention is assessed using Courneya’s [88] recommendation for open-scaled measurement. Attitudes toward engaging in parent-child co-activity are measured with items covering both affective and instrumental components [89, 90], and items related to ability for parent-child co-activity assess perceived capability [91, 92]. An instrument adapted from Sniehotta and colleagues [93] assesses behavioural regulation. Lastly, items adapted from Anderson and Cychosz [94] measure identity. All of these instruments have previous application in various populations and have demonstrated previous strong predictive validity and internal consistency evidence scores among adults [95–97], and with parental physical activity support. Finally, the measures have shown some prior validity evidence for family-based physical activity as well as personal physical activity [30, 73].

#### Other parental factors

Several additional parental factors are assessed at all measurement points (baseline, 6 weeks, 3 months, and 6 months). Namely, instruments that have shown adequate validity and reliability in prior test scores measure the following: quality of life is determined via the 12-item Short-Form Health Survey [98]; parental competence is assessed with the Parenting Sense of Competence Scale [99]; and family functioning is assessed through the Family Environment Scale [100].

#### Demographics

A section of the baseline questionnaire assesses various demographic characteristics including gender, age, ethnicity, level of education, marital status, employment information, household income, and health background.

#### Manipulation check outcomes

To examine the manipulation check outcomes, items assessing parental self-report of the utilization of context-dependent repetition/cues and consistency/repeated action are used [38]. These measures take place at all measurement time points. For the measure of context-dependent repetition/cue utilization, parents are presented with the phrase “each time I am physically active with my child” and are asked to rank six statements on a seven-point scale from “not true at all” to “very true”. The statements incorporate temporal (‘it was the same time of day’), visual (‘I was in the same place’), social (‘I was around the same people’), and mood (‘I was in the same mood’) aspects. The single item consistency of practice measure asks parents “how consistently are you physically active with your child at the same time each day?” with answers on a five-point scale ranging from not consistent to very consistent. This measure assists with understanding repeated action and is therefore a reasonable assessment of the utilization of key habit formation techniques.

Additionally, parents complete a short process evaluation of the intervention in the six-month questionnaire. First, a brief questionnaire assesses use of the intervention materials and satisfaction with the study [101]. Finally, semi-structured interviews pertaining to types and frequency of co-activity, barriers, outcomes, intervention material use and study satisfaction are conducted at the end of the trial, in order to gain rich, in-depth program evaluation data that has proved useful in prior trials [34]. These interviews will also incorporate simple quantitative questions regarding the use and ease of the intervention materials.

### Analysis strategy

For each outcome, the pattern of missing data will be evaluated to determine an appropriate analytical strategy [102], after which the normality of all variables will be examined to determine whether transformations will be required. The first set of analyses will make preliminary demographic comparisons among adherers to the study versus dropouts to determine the representativeness of the sample. Next, to address the primary objective (i.e., to determine whether the minutes / day of MVPA change over time similarly for all three conditions, hierarchical linear modeling [103] will be used. Specifically, Level-1 of the model will include an intercept (i.e., the baseline PA) and slope (i.e., to examine potential change over the 4 assessment periods) that will be predicted by Level-2 covariates (i.e., demographics). Additionally, dummy variables will be created for condition (Habit formation group: 1 = yes or 0 = no; Planning group: 1 = yes or 0 = no; Education control: 1 = yes or 0 = No) at Level-2 with the Habit Formation and Planning group variables being added to the model to predict the intercept and slope at Level-1. In doing so, the control group is compared against the other two groups to determine if baseline MVPA is similar across conditions and whether the change in MVPA is similar across conditions. Follow-up analyses will be conducted for the Habit Formation vs. Planning group comparison. To address the secondary objective (i.e., to determine whether the change in the underlying motives explain the potential change in MVPA during the intervention similarly for all 3 groups), a time varying covariate mediation analysis will be used [104]. Briefly, the analyses needed to establish mediation will treat the underlying motives as time varying covariates at Level-1 of the model. Then, the dummy coded condition variables will be entered at Level-2 to determine if the Level-1 motives mediate the condition / MVPA relationship. Finally, to determine whether there is a seasonal, intergenerational, or gender difference across the primary and secondary outcomes (i.e., to address the tertiary objectives), each variable will be entered into the various models at Level-2 to predict the intercepts and slopes at Level-1. Doing so will determine if they impact the change in the various outcomes across time.

Qualitative data analysis will be conducted by research assistants independent from the intervention activities and will be overseen by the principal investigator. This component of intervention evaluation will draw from a qualitative social constructionist perspective [105] to understand in the parents’ own words, the beneficial features and any problematic components of the intervention. Data collected via the semi-structured interviews will be analysed through use of inductive content analytic procedures [106], facilitated by the NVivo software program. Themes will be identified that correspond to the strengths and limitations of the intervention program. The response themes will also be linked at the individual level, so post-hoc assessment of successful and unsuccessful interventions can be examined by these responses.

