### Study objectives and hypotheses

The primary objective of this study is to investigate the effects of a theory-based intervention targeting parent-child co-activity to promote child MVPA (primary outcome) across 6 months. Namely, the effect of a *habit formation* (context-dependent repetition from prompts and cues, consistent practice) and planning and education condition (action planning, coping planning, and information on benefits), will be compared against a *planning* and education condition (action planning, coping planning and information on benefits) and a standard *education* condition (information on benefits) on child PA. Consistent with previous research [30, 46], it is hypothesized that the habit formation intervention targeting parent-child co-activity will yield greater increases in co-activity and subsequently influence objectively measured child MVPA at 6 months (primary end-point) compared to those in the planning and education conditions. Further, based on extant research on the efficacy of planning interventions among families [34], we predict that children in the planning condition will show greater increases in MVPA compared to the education-only group because planning aids PA adoption, however these initially efficacious effects will wane over time due exhausting nature of constant volitional planning and the lack of strategies to assist with maintenance.

The secondary objective will be to explore group differences among behavioural outcomes using a mediation model. We hypothesize that child PA will be influenced by parent-child co-activity, which will be a result of PA support from parents in the form of co-participation. Higher PA support (co-participation) is expected to come from those in the habit formation condition, followed by self-regulatory planning compared to education. Thus, it is hypothesized that the covariance of the assigned condition (habit formation, planning, and education) will be explained by parental co-activity habit strength through the use of context repetition/cues and consistency/repeated action (i.e., manipulation check).

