### Design

This study is a randomized trial with a single-blinded, three-arm parallel design. Upon the completion of baseline measures (questionnaire, accelerometer wear) participants are assigned to one of three groups: 1) standard co-activity education (education condition); 2) co-activity education and planning (planning condition); 3) co-activity education, planning, and habit formation (habit formation condition). The main outcome measure of child MVPA (dependent variable) will be assessed at the primary end point of the trial (6 months) with secondary assessments time points at 6 weeks and 3 months.

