
### Outcome measures

#### Primary outcome measures

The primary outcome of child MVPA will be assessed with the Actigraph wGT3X-BT Activity Monitor using validated seven-day accelerometry methods for preschoolers. Measurements will take place at baseline, 6 weeks, 3 months, and 6 months (primary endpoint of interest) and MVPA will be evaluated as change from baseline. Currently, the analysis plan is to use the established cut-points and accelerometer best practices outlined below, however the research team recognizes that accelerometer analysis in an ever-changing discipline, therefore we will be responsive to these advances by using the most validated cut-points at the time of study closure. At present, it is anticipated that the MVPA of children will be determined using the cut-points for young children recommended by Janssen and colleagues [63]. These cut-points define moderate to vigorous activity as ≥420 counts per 15 s (≥1680 counts per minute (CPM)). These cut-points have shown fair to excellent validity in preschoolers when compared to direct observation [63].

Children are instructed to wear the device during waking hours for a minimum of 10 h a day for 7 consecutive days (5 weekdays, and 2 weekend days). It is secured by an elastic band and worn around the waist above the right hip. Because the devices are not waterproof, participants are advised to remove them for any water-based activities. In addition, participants are provided with a logbook and parents are asked to note any removals for water activities, record unusual circumstances (e.g., changes to routine such as illness), and make notes with particulars such as structured activity.

To initialize and download the accelerometers as well as analyze the data, ActiLife software version 6.11.9 [64] is used. The devices are initialized to collect data at a 30 Hz sample rate and are downloaded into 15-s epochs in order to capture the sporadic nature of movement in young children and based on common practice for preschooler accelerometry [65, 66]. Data will be included for analysis if children have at least 4 days of valid wear time per week [67–69]. For a day to be considered valid there will need to be a minimum of 300 min (6 h) during waking hours [70]. Non-wear time is defined as ≥20 min of consecutive zero counts or the equivalent of ≥80 consecutive 15-s intervals of zero counts [69, 71]. It is assumed that this non-wear time algorithm captures daytime naps.

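### The primary endpoint is 6-month change in child MVPA, but the stated primary model tests one slope per condition, which equals that contrast only if change is linear

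*Protocol article*

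**What the plan says.** For the primary objective, the Analysis strategy section specifies hierarchical linear modelling: "Level-1 of the model will include an intercept (i.e., the baseline PA) and slope (i.e., to examine potential change over the 4 assessment periods"). Treatment enters through the "Habit Formation and Planning group variables being added to the model to predict the intercept and slope at Level-1". The section adds that "the control group is compared against the other two groups to determine if baseline MVPA is similar across conditions", and that change is compared in the same way. Habit versus planning is a follow-up comparison. The section names no curved, piecewise or categorical time term, no coding of time and no 6-month contrast.

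The endpoint is fixed elsewhere. Under Design, child MVPA "will be assessed at the primary end point of the trial (6 months) with secondary assessments time points at 6 weeks and 3 months". Primary outcome measures states "Measurements will take place at baseline, 6 weeks, 3 months, and 6 months (primary endpoint of interest") and that "MVPA will be evaluated as change from baseline".

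Study objectives and hypotheses places the habit hypothesis at 6 months. It expects planning to beat education at first, "however these initially efficacious effects will wane over time". The Background reports the same pattern from an earlier planning trial: a gain at 6 weeks that faded.

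**The concern.** The endpoint is a contrast at one visit. The stated test is a difference in slope across four unevenly spaced visits. The two agree when change is linear, but the protocol predicts another shape for planning.

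An early gain that fades pulls the fitted line down at the end and up at the start. The slope then misstates the 6-month effect, and the lack of fit appears in the intercept as a baseline gap. The plan reads that intercept as a check on baseline similarity, although allocation follows the baseline measures and is random. One slope per condition also has no term for a rise followed by a fall, so the waning hypothesis goes untested in the model as stated.

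**Working it through.** **The plan's own figure.** The sample size can be reproduced as a one-way comparison of three groups at power 0.90 and alpha 0.05: N = 144 at effect size 0.30 and 207 at 0.25. Multiplying by 1.15 gives 166 and 239, against the stated 165 and 240. That calculation uses neither the slope nor the four assessments, so it does not settle this point.

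**Inputs.** Visits are at 0, 6 weeks, 3 months and 6 months (Primary outcome measures), taken as weeks 0, 6, 13 and 26. Time coding is not stated, so visit number (0 to 3) is also shown. The curves are assumptions.

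**Formulas.** Slope = Σ(t − t̄)y / Σ(t − t̄)². The slope-implied 6-month effect is the slope times the full time span. The fitted baseline gap is ȳ − slope × t̄.

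- Weeks: t̄ = 45/4 = 11.25; deviations −11.25, −5.25, 1.75, 14.75; sum of squares 374.75; span 26.
- Visit number: t̄ = 1.5; deviations −1.5, −0.5, 0.5, 1.5; sum of squares 5; span 3.

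**Worked case, planning minus education 0/10/5/0.**

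- Weeks: (−52.5 + 8.75)/374.75 = −0.117 per week; × 26 = −3.0. Baseline gap 3.75 + 0.117 × 11.25 = +5.1.
- Visit number: (−5 + 2.5)/5 = −0.5; × 3 = −1.5. Baseline gap 3.75 + 0.75 = +4.5.

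**All cases (min/day).**

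| Assumed difference | True at 6 months | Weeks | Visit number |
|---|---|---|---|
| Planning − education 0/10/5/0 | 0 | −3.0 | −1.5 |
| Planning − education 0/10/7.5/5 | 5 | +2.4 | +3.8 |
| Habit − education 0/10/10/10 | 10 | 7.8 | 9.0 |
| Habit − education 0/1/4/10 | 10 | 10.4 | 9.9 |
| Habit − planning 0/0/5/10 | 10 | 10.8 | 10.5 |

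With complete data, adding random intercepts or slopes does not change these fixed effects.

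**When the sign is wrong.** Let the planning effect be 1 at 6 weeks, a at 3 months and b at 6 months. In weeks, the slope-implied effect is −0.364 + 0.121a + 1.023b. It is negative when b is below 0.26 (a = 0.8) to 0.32 (a = 0.3). By visit number it is −0.3 + 0.3a + 0.9b, with limits 0.07 to 0.23.

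**Effect on the test.** Assume a 6-week effect of 0.5 SD, equal correlation 0.5, time in months and 47 analysed per arm (165 × 0.85 / 3 = 46.75).

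- Early, held effect: power 53% for the slope, 68% for the 6-month change contrast.
- Planning effect waned to zero (0/1/0.5/0 times d): the slope test rejects 11% of the time, against a nominal 5%.
- Exactly linear change: the slope does better, 72% against 68%.

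**Precision of the 6-month contrast** (units sigma²/n, equal correlation r, time in weeks).

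| Model | Formula | r = 0.3 | r = 0.5 | r = 0.7 |
|---|---|---|---|---|
| Slope, free intercept (as written) | 2(1 − r) × 676/374.75 | 2.53 | 1.80 | 1.08 |
| Categorical visit, free baseline | 4(1 − r) | 2.80 | 2.00 | 1.20 |
| Categorical visit, common baseline | 2(1 − r²) | 1.82 | 1.50 | 1.02 |
| Slope, common baseline | 2 × 676 / t′V⁻¹t | 1.69 | 1.42 | 0.96 |

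For the last row at r = 0.5, t′V⁻¹t = 2 × (881 − 0.2 × 2025) = 952, and 1352/952 = 1.42.

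At equal baseline handling, categorical visit costs 2.00/1.80, or 11%, with a free baseline and 6 to 8% with a common one. By visit number at r = 0.5, the common-baseline slope has variance 18/13.6 = 1.32, so the cost there is about 13%.

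**The case against.** The strongest reply is that the article also frames its primary objective as change over time by condition. The Analysis strategy introduces the model that way, and the sample-size section aims at a difference by condition over time. A slope test answers that framing. This stands: the conflict is between two statements of the primary question, and a reader who infers that the test answers neither goes too far.

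Other points also stand. The hypotheses say that planning effects wane, not that they vanish, so a reversed sign needs near-complete waning, and it arises only for planning versus education. The intervention text calls the habit condition the one of key interest, and on the curves above habit versus planning keeps its sign and is only 5 to 8% too high. No time path is given for habit, so a reader might infer that its effect will be understated, but a gradual build-up shows little bias. A condition term on the intercept is a standard growth-model choice. A common baseline is more efficient, but a free one is not in itself an error.

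The reply that an analysis plan could add terms carries less weight. The article states the Level-1 terms and the condition effects on them, and those do not match its endpoint. It does mean that one cannot say the trial is unable to test waning. Only the stated single-slope model fails to do so.

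**Conclusion.** The concern holds as a mismatch between a stated model and a stated endpoint. Its size depends on the shape of the effect and on time coding, which the article does not give. On the assumed curves, planning versus education is off by 1.2 to 3.0 min/day for a 6-week effect of 10 (5 − 3.75 under milder waning by visit number, up to 0 − (−3.0) under full waning in weeks). Full waning also produces a false baseline gap of about 4.5 to 5 min/day. An early, held habit effect is understated by 10 to 22%. Gradual habit growth and habit versus planning are little affected.

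A reader might infer that the primary result will come out with the wrong sign. The documents do not support that: it needs strong waning and concerns one of the three comparisons. A reader might also infer that categorical visit is free in precision. It is not: at equal baseline handling with time in weeks it costs about 6 to 11% in variance, and the net gain over the plan as written comes from the common baseline.

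**What to change.** Before outcome data are analysed, restate the primary model as follows.

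- Use a mixed model with visit as a categorical factor, condition-by-visit terms at 6 weeks, 3 months and 6 months, and one baseline mean common to the three arms (or baseline MVPA as a covariate).
- Make the 6-month between-arm contrast in min/day the primary test.
- Test waning as the planning-minus-education contrast at 6 weeks minus the same contrast at 6 months.
- Drop the test of baseline MVPA between arms.
- Keep the slope model as supportive, with its time coding stated.
- Align the wording of the primary objective in the Analysis strategy and sample-size sections with the 6-month endpoint.

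The cost is a change of wording and a few more fixed-effect parameters. No data collection changes. Categorical visit gives up some efficiency if change really is linear, in exchange for removing the dependence on shape.

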### Randomization

Simple randomization is done by the Project Coordinator using computer-generated random numbers in an Excel spreadsheet. Allocation is concealed from the enrolment and assessment team by the Project Coordinator. Upon completion of baseline measures, condition allocation is communicated to the intervention delivery team so as to allow for the correct delivery of materials. Participants are blind to their condition until study completion, at which point they are notified of their allocation by the research team and provided with any additional materials they did not originally receive.

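### Condition is allowed to predict the pre-randomisation baseline, so the between-arm slope contrast is unbiased but less precise than it could be at no cost

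*Protocol article*

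**What the plan says.** Under Analysis strategy, the primary model is a hierarchical linear model over four assessments: "Level-1 of the model will include an intercept (i.e., the baseline PA) and slope". The condition indicators enter in two places, with the "Habit Formation and Planning group variables being added to the model to predict the intercept and slope at Level-1". The stated use of the intercept terms is that "the control group is compared against the other two groups to determine if baseline MVPA is similar across conditions". The model terms are ones "that will be predicted by Level-2 covariates (i.e., demographics"; baseline MVPA is not named as a covariate, and no common baseline mean is stated.

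Under Primary outcome measures, "MVPA will be evaluated as change from baseline".

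On timing, the Design section says "Upon the completion of baseline measures (questionnaire, accelerometer wear) participants are assigned to one of three groups", and Randomization says "Upon completion of baseline measures, condition allocation is communicated to the intervention delivery team". The Procedures and protocol section agrees: baseline wear, then the accelerometry screen, then randomisation. The method is also stated: "Simple randomization is done by the Project Coordinator using computer-generated random numbers in an Excel spreadsheet".

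**The concern.** Baseline MVPA is fixed before allocation. Any difference between arms at baseline is therefore chance, and the arms' expected baseline means are equal without further assumption. A model with a free intercept per arm estimates two differences that are known to be zero in expectation, and the slope contrast pays for it. A chance baseline difference is carried into the estimated difference in change instead of being partly discounted.

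Simple randomisation does nothing to limit such differences. At the planned minimum of 55 families per condition, the standard error of a between-arm baseline difference is sqrt(2/55) = 0.19 SD before any attrition.

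At stake is the width of the interval for the primary contrasts, including habit versus planning. The Justification of sample size section itself says that detecting this difference depends on performance that is largely unknown. The comparison of baselines by arm is uninformative, because it examines a null hypothesis that is true by design.

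**Working it through.** **Does the stated sample size depend on this choice?** Inputs from Justification of sample size: 3 groups, alpha 0.05, power 0.90, effect sizes 0.25 to 0.30 (read as Cohen's f), 15% attrition. A one-way ANOVA with noncentrality N f² needs 144 families at f = 0.30 and 207 at f = 0.25. Multiplying by 1.15 gives 165.6 and 238.05, close to the stated 165 and 240. That calculation credits no baseline correlation, so the stated numbers do not depend on how baseline is modelled.

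**Slope contrast, free versus common baseline.** Assessments are at 0, 1.5, 3 and 6 months (six weeks taken as 1.5 months). Mean time is 10.5/4 = 2.625. The sum of squared deviations is S = 19.6875. Take unit variance at each visit and a constant correlation rho between visits (compound symmetry). Neither is in the article; rho is assumed at 0.4 to 0.7.

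- Free baseline per arm: only within-family deviations inform the difference in slopes, so its variance is proportional to (1 − rho)/S.
- Common baseline: the family mean also carries slope information. Its variance is (1 + 3 rho)/4, so the contrast variance is proportional to 1 / [S/(1 − rho) + 2.625² × 4/(1 + 3 rho)].
- Since 2.625²/S = 6.890625/19.6875 = 0.35, the ratio of common to free is 1 / [1 + 1.4 (1 − rho)/(1 + 3 rho)].

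| rho | 1.4(1 − rho)/(1 + 3 rho) | variance ratio | variance saved |
|---|---|---|---|
| 0.4 | 0.84/2.2 = 0.382 | 0.72 | 28% |
| 0.5 | 0.70/2.5 = 0.280 | 0.78 | 22% |
| 0.6 | 0.56/2.8 = 0.200 | 0.83 | 17% |
| 0.7 | 0.42/3.1 = 0.135 | 0.88 | 12% |

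A generalised least squares calculation with all three arms gives the same ratios, for each arm against education and for habit against planning. In standard errors the saving is 1 − sqrt(0.72) = 15% down to 1 − sqrt(0.88) = 6%.

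**Random intercept and slope.** Five sets of assumed variance components, with baseline to 6-month correlations of 0.34 to 0.55, give ratios of 0.73, 0.79, 0.84, 0.87 and 0.93. The smallest saving, 7%, arises when intercept and slope are positively correlated (0.3).

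**Narrowed baseline.** Participants and eligibility restricts entry to children below guideline. Suppose, as an assumption, that this halves baseline variance and leaves the regression of follow-up on baseline unchanged. The baseline variance becomes 0.5, its covariance with each follow-up 0.5 rho, the follow-up variance 1 − 0.5 rho², and the covariance between follow-ups rho − 0.5 rho², where rho is the unscreened value. The slope-contrast ratios become 0.82, 0.87, 0.90 and 0.93 for rho 0.4, 0.5, 0.6 and 0.7, a saving of 18% down to 7%.

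The gain was positive in every case computed.

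**The case against.** The planned model is a conventional and valid growth model. Under randomisation its slope contrast is unbiased, and chance baseline imbalance is already reflected in its standard error. The sample size does not rest on this choice. The article sets no significance threshold for the baseline comparison and makes no later step depend on it. The change-from-baseline wording names an outcome scale, and a common-baseline model also estimates change from baseline. All of this stands. It limits the point to efficiency, and it means that the two sections describe one loss, not two.

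A reader might infer more in three ways that the documents do not support.

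- *A two-point change score.* The familiar ratio (1 + rho)/2 gives a 25% variance saving at rho = 0.5, and so about a third more families for the same precision. It assumes equal variances and a comparison of baseline with 6 months alone. Analysis strategy plans a slope over four assessments, so that figure is not the right size here.
- *Range restriction.* The screen may seem to enlarge the loss by lowering the correlation. It works the other way. The excess variance of a change score over an adjusted score is (1 − b)² × Var(baseline), where b is the regression slope on baseline. A narrower baseline shrinks it.
- *Regression to the mean.* Children selected for low baseline activity will tend to rise in every arm, but this is common to the randomised arms and cancels in the contrast. The proposed change would not remove it from within-arm trends.

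A separate analysis plan might refine the model. The intercept terms and their purpose are nevertheless stated in the article, so this is not a matter of missing detail.

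**Conclusion.** The point holds as a matter of precision, not validity. For an assumed rho of 0.4 to 0.7, the planned parameterisation gives up about 12% to 28% of the variance of the between-arm slope contrast under compound symmetry. The loss may be as little as about 7% with random slopes or a narrowed baseline. The direction is firm because allocation follows baseline measurement. The size is not, because rho, the covariance structure and the effect of the screen are all assumptions. The figures also take the straight-line time trend as planned, with time in months; equal-step visit coding would give ratios of 0.67 to 0.85 over the same rho range. The change is worth making because it costs nothing, but the trial is not invalid without it.

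**What to change.** In Analysis strategy, remove the condition terms from the intercept so that all arms share one baseline mean and condition enters only through its time terms (constrained longitudinal analysis). Alternatively, model the follow-up visits only, with baseline MVPA as a covariate. Delete the model-based comparison of baseline MVPA between arms and report baseline MVPA by arm descriptively. Under Primary outcome measures, reword the change-from-baseline statement so that it names the same analysis.

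The cost is analysis wording only. The data are already collected under the plan, and neither the sample size nor trial conduct changes. The amendment should be dated before unblinded outcome data are examined.
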